**Fig. 2 Fig2:**
[figure not shown]
Diagram of the patient flow through the study

Randomization will be conducted by permuted blocks and an independent staff will prepare consecutively numbered, sealed envelopes. The physiotherapists and nurses who execute the baseline and follow-up testing will be blinded for the randomization. The patients and the three physiotherapists delivering the pain coping education cannot be blinded.

### Preoperative screening and selection of “high Pain Catastrophizing” patients

Patients will be screened preoperatively at the outpatient clinic after they are scheduled for a TKA using the questionnaire Pain Catastrophizing Scale (PCS) [27]. PCS consists of 13 questions where the patients rate their thoughts and feelings when they are experiencing pain. The total score is ranging from 0 indicating no “pain catastrophizing” to 52 indicating worst “pain catastrophizing”. Each item are rated on a 5-point scale ranging from “not at all” to “all the time”. The Danish version of PCS is considered valid for use in clinical pain samples and the internal consistency is found acceptable [28].

The cut-off score for PCS is chosen on basis of data collected in the years 2011–2013 at Holstebro Regional Hospital. 530 TKA patients answered the PCS before the operation. Median PCS score was 16 range (0–52). In the present trial we want to include the 33% of our TKA population with the highest PCS score. This means that we will use the 66th percentile of the total score to define the cut-off in this study. Thus, patients with a PCS score on 23 or higher are eligible for inclusion and in this study defined as patients with “high pain catastrophizing”.

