### Participants and recruitment

We will recruit 56 patients from the Orthopedic outpatient clinic at Holstebro Regional Hospital.

To be eligible for inclusion the patients must fulfill the following criteria:Be able to speak, talk and understand Danish language.Provide informed consent.Have a primary diagnosis of osteoarthritis.Be scheduled for an elective unilateral total knee arthroplasty.Age ≥ 18 years.A score >22 on the Pain Catastrophizing Scale (PCS).

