### Exclusion criteria

Severe depression (at least three core symptoms and two accompanying symptoms) diagnosed with the Major Depression Inventory (MDI) [26].Scheduled for revision arthroplasty.Scheduled for a unicompartmental arthroplasty.Planning to have a contralateral knee arthroplasty within 1 year from the operation.Have a diagnosis of inflammatory arthritis.

Patients eligible for participation will be randomized into the two arms, usual care or patient education (Fig. 2). The patients will not be aware of the study hypotheses and will not be informed about the association between a high PCS score and long-term pain after TKA. The randomization will take place approximately 2–3 weeks before the operation. Because the time between the patients are scheduled for operation by the surgeon and the operation is very short (2–3 weeks) the patients will be randomized immediately after they are included and before baseline assessments to be able to make three pre-operative appointments with the patients in the intervention group.

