### Outcome assessment

The data presented in Table 2 will be measured before the operation and 3 and 12 months postoperative. Physical function and DXA scan will be measured during clinic visits. All the self-reported questionnaires are send by e-mail or post to the patients 2 weeks before the visit together with the tri-axial accelerometer. The primary outcome measure of the study is the 100-mm Visual Analogue scale (VAS), which is a self-reported pain measurement ranging from 0 indicating “no pain” to 100 indicating “worst pain imaginable” [31].

**Table 2 Tab2:** Primary and secondary outcome measures

Measure	Instrument	Collection points and method
Primary outcome:		
Self-reported Pain intensity	Visual Analogue Scale (VAS)	Baseline, 3 and 12 months follow up by post/email
Secondary outcomes:		
Self-reported function	SF-36 Physical Function	Baseline, 3 and 12 months follow up by post/email
Self-reported function and pain	Oxford Knee Score (OKS)	Baseline, 3 and 12 months follow up by post/email
Self-reported health status	EQ-5D-3 L	Baseline, 3 and 12 months follow up by post/email
Self-reported pain catastrophizing	Pain Catastrophizing Scale (PCS)	Baseline, 3 and 12 months follow up by post/email
Self-reported daily function and quality of life	Knee injury and Osteoarthritis Score (KOOS)	Baseline, 3 and 12 months follow up by post/email
Self-reported pain self-efficacy	Pain Self-Efficacy Questionnaire (PSEQ)	Baseline, 3 and 12 months follow up by post/email
Daily activity	Tri-axial accelerometer	Baseline, 3 and 12 months follow up by post/email
Physical function	6 min’ walk test (6MWT)	Baseline, 3 and 12 months follow up test in clinic
Physical function	Sit to stand 30 s. (STS30)	Baseline, 3 and 12 months follow up test in clinic
Muscle mass and bone mineral density	DXA scan	Baseline, 3 and 12 months follow up scan in clinic
Other measures		
Healthcare visits	Self-report (log book)	0–3 months’ post-operative at home
Smoking	Self-reported questionnaire	Baseline, 3 and 12 months follow up by post/email
Pain killers	Self-reported questionnaire	Baseline, 3 and 12 months follow up by post/email
Alcohol	Self-reported questionnaire	Baseline, 3 and 12 months follow up by post/email
Education	Self-reported questionnaire	Baseline, 3 and 12 months follow up by post/email
Social status	Self-reported questionnaire	Baseline, 3 and 12 months follow up by post/email

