### Sample size and statistical analysis

The primary outcome measure will be VAS under activity measured on a continuous 100 mm scale 12 month after the operation. Clinically important differences between the two groups is detected to be 18 mm [46, 47]. Based on earlier studies we assume a common standard deviation between participants of 19 mm on VAS [2, 10, 48]. With a significance level at 0.05 and the power at 0.90 the study needs 23 patients in each arm. Taking into account a loss to follow-up after 1 year on approximately 20% we aim at including 28 patients in each group a total of 56 patients.

Clinical and demographic characteristics as well as baseline data will be presented to show the baseline comparability of the two groups. Data from the patients who withdraw from the study will also be examined. For each group descriptive statistics will be presented at baseline and three and 12 months postoperative. Normally distributed data are described by means and standard deviation (SD), and data not normally distributed by medians and interquartile range (IQR). The primary analysis will use the intention-to treat principle including all randomised participants. Patients who discontinue the intervention will be encouraged to participate in the follow up test anyway, and those who accept will be included in the analyses according to their original group assignment. The primary outcome pain is measured on a continuous scale and between-group mean differences and 95% confidence intervals from baseline to 3 and 12 months will be analyzed by a mixed effects linear regression model with a random person level and systematic effects of time, group and the interaction between time and group. We will employ multiple imputation methods in order to assess the sensitivity of the mixed model to any informative missing values. Imputations will be performed using baseline characteristics and non-missing pain measurements on individual levels. Secondary outcomes will be analysed as above for normally distributed measures or for binary outcomes, we will use logistic regression with a robust variance estimate to account for the repeated measurements. Standard diagnostic plots will check model assumptions. The statistical analyses will be performed using STATA 13 (StataCorp, College Station, TX) software package. The significance level will be set at 0.05.

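### The PCS outcome is measured as change from a questionnaire completed after unblinded allocation, although every randomised patient already has a pre-randomisation PCS that could serve as baseline covariate

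*Protocol article*

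**What the plan says.** - **Screening score.** The section on preoperative screening states: "Patients will be screened preoperatively at the outpatient clinic after they are scheduled for a TKA using the questionnaire Pain Catastrophizing Scale (PCS". Under Participants and recruitment, eligibility requires "A score >22 on the Pain Catastrophizing Scale (PCS".
- **Order.** Under Exclusion criteria, "the patients will be randomized immediately after they are included and before baseline assessments". The reason given is the 2–3 week window in which three pre-operative sessions must be booked.
- **Blinding.** The paragraph on randomisation below Fig. 2 says: "The patients and the three physiotherapists delivering the pain coping education cannot be blinded".
- **Outcome baseline.** Under Outcome assessment, Table 2 has a secondary-outcome row "Self-reported pain catastrophizing" collected at "Baseline, 3 and 12 months follow up by post/email". The text adds: "All the self-reported questionnaires are send by e-mail or post to the patients 2 weeks before the visit together with the tri-axial accelerometer". This is a separate administration from the one in clinic.
- **Analysis.** The primary model is a linear mixed model with time, group and their interaction, giving between-group differences from baseline to 3 and 12 months. Then: "Secondary outcomes will be analysed as above for normally distributed measures".
- **Disclosure.** The Discussion lists randomisation before baseline assessment as a limitation. It argues that this should not matter because patients are not told of the link between PCS and long-term pain.

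The article gives the screening score no role beyond eligibility.

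**The concern.** A baseline used to measure change should not be open to influence by the treatment assignment. The mailed PCS is: it is self-reported, it follows randomisation, and the patient knows whether pain-coping sessions have been offered. Withholding the link between PCS and later pain does not hide that knowledge, so the argument in the Discussion leaves the problem in place.

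Lower catastrophizing is the fourth hypothesis, and catastrophic thinking is what the education sets out to change. A distorted baseline would distort the estimate of that effect. For this outcome, unlike the others, a value of the same instrument taken before randomisation already exists for everyone.

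**Working it through.** **1. Order of measurements, from the text.** PCS in clinic → eligibility (score of 23 or more) → randomisation → allocation known → PCS by post or e-mail (Table 2 baseline) → surgery → PCS at 3 and 12 months. The first score cannot depend on the arm; the second can.

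**2. The plan's own figure.** The plan gives no SD, effect or sample size for PCS. Its only calculation is for VAS: 2 × [19 × (1.960 + 1.282) / 18]² = 23.4 per arm, against 23 stated. Nothing below depends on it; only the 28 per arm is carried over.

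**3. What the planned contrast estimates.** The group effect is free at baseline, so with complete data the time-by-group term is

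estimate = (follow-up mean, intervention − control) − (mailed baseline mean, intervention − control).

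If knowing the allocation lowers the mailed baseline in the intervention arm, relative to control, by *s* points, then estimate = true effect + *s*. With an assumed true effect of -5:
- *s* = 0: -5 + 0 = -5
- *s* = 2: -5 + 2 = -3
- *s* = 4: -5 + 4 = -1

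A relative shift the other way would exaggerate the effect by the same amount.

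**4. Simulation.** Assumptions, none of them from the documents: PCS mean 17, SD 13, reliability 0.70 or 0.85, true effect -5, shift *s* of 0, 2 or 4 points. Patients are selected at PCS above 22, with 28 per arm and 6,000 replicates. As a plausibility check on mean and SD, the normal 66th percentile is 17 + 0.412 × 13 = 22.4, in line with the cut-off of 23 that the protocol takes from its own 66th percentile.

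| Mean estimate (reliability 0.70 / 0.85) | s = 0 | s = 2 | s = 4 |
|---|---|---|---|
| Change from mailed PCS (planned) | -5.00 / -5.04 | -3.00 / -2.97 | -1.00 / -1.06 |
| Follow-up adjusted for mailed PCS | -5.02 / -5.06 | -4.26 / -4.02 | -3.50 / -3.12 |
| Follow-up adjusted for screening PCS | -5.03 / -5.05 | -4.99 / -4.99 | -4.96 / -5.04 |

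Adjusting for the mailed score removes only part of the bias. Adjusting for the screening score removes it.

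**5. Precision.** Standard errors at *s* = 0 (reliability 0.70 / 0.85): change from mailed PCS 2.87 / 2.10; adjusted for screening PCS 2.36 / 1.72; adjusted for mailed PCS 2.29 / 1.68.
- Screening adjustment against the planned contrast: 1 − 2.36/2.87 = 18%, and 1 − 1.72/2.10 = 18%.
- This set-up favours adjustment, because follow-up true scores shrink towards the mean with no fresh variation. When true scores are instead allowed to drift between visits (stability 0.5–1.0), the saving is roughly 2–16%.
- Screening against mailed PCS, both as covariates: no gain; the mailed score is slightly better (2.29 against 2.36, 1.68 against 1.72).

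The saving therefore comes from covariate adjustment in place of a change score, not from the choice of score.

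**6. Truncation.** In the simulation the selected patients average 31.1 on the screening score, while their true mean is 26.9 (reliability 0.70) or 29.0 (0.85). Apparent improvement of 31.1 − 26.9 = 4.2 or 31.1 − 29.0 = 2.1 points would occur in both arms with no treatment at all. It cancels between arms, as the last row of the table shows.

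**The case against.** **The authors disclose the order of events and explain it.** True, and the short window is a fair reason for it. But disclosure does not remove the bias, and here a remedy is already in hand.

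**A reader might infer that session one contaminates the mailed PCS.** The documents do not support this. The Discussion names only the DXA scan, the sit-to-stand test and the walk test as following session one, and excuses them as not patient-reported. That suggests the questionnaires come earlier. No return deadline is stated, so it is not excluded, but the point needs only knowledge of allocation.

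**A reader might infer that the plan rules out the screening score.** It does not say so, and a condensed article may leave covariates to a fuller document. What stands is what the article does fix: a post/e-mail baseline, collected after randomisation, and a contrast measured from it.

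**A reader might infer a known bias that understates the benefit.** Neither size nor direction can be had from the documents. Hopeful or disappointed patients could shift either arm's score.

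**A reader might prefer the screening score for precision or completeness.** The precision argument fails (step 5). Completeness carries little weight, since the mixed model uses partial data and multiple imputation is planned.

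**The mailed score has merits.** It is not truncated directly by the selection and is collected in the same way as follow-up. This stands, and is why it should be kept.

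**It is one secondary outcome among several.** This also stands. It limits the weight of the point.

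**Conclusion.** The point holds for the PCS outcome. As written, the plan measures change from a self-report made after unblinded allocation, and any relative shift in that score enters the estimate in full: 2 points of shift means 2 points of bias on the 0–52 scale. Whether a shift will occur is not known; the 0–4 point range and the -5 point effect are assumptions used to show the mechanism. That adjusting for the screening score is free of this bias rests only on that score preceding randomisation, which the text establishes. The standard error saving of roughly 2–16% against the planned contrast depends on assumed reliability and stability and is a secondary benefit.

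The primary VAS outcome and the sample size are untouched. No VAS before randomisation is described, so the same remedy is not available there. This is a worthwhile improvement to a secondary analysis, not a threat to the trial's main conclusion.

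**What to change.** In Sample size and statistical analysis, give PCS its own sentence. The 3- and 12-month scores are the responses in the mixed model, with group, time and their interaction, a random person effect, and the screening PCS as baseline covariate. The arm difference is estimated at each visit, with no contrast of change from the mailed baseline. In Table 2, distinguish the screening PCS (before randomisation) from the mailed pre-operative PCS. Retain the latter for description and for a sensitivity analysis that uses it as the baseline.

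The cost is wording only: no new data, visits or patients. The one drawback is that the screening score is truncated at 23 or higher, so within-arm change from it includes regression to the mean and should not be presented as improvement. The between-arm comparison stays unbiased.

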### Control group

Patients in the control group will receive usual care. This consists of a multidisciplinary information meeting for patients and their relatives, approximately 1 week before the operation. After the operation the patients have contact with the hospital 4 times. Seven days (telephone call), 14 days, 4 weeks and 3 months after the operation they will be called in for a control visit with the nurse, physiotherapist and operating surgeon respectively. Further, some of the patients will receive physical rehabilitation in their local community.

### Intervention group

The intervention group will in addition to the described usual care participate in a patient education based on cognitive-behavioral therapy. We wanted to design a patient education that fits into a hospital setting with relatively few session contrary to previous studies were the CBT intervention most commonly range from 10 to 12 sessions [20, 23, 29]. Our patient education consists of seven individual sessions. Three sessions before the operation and four after. A similar trial has recently shown similar amounts of sessions to be effective [24]. Except session one and three all the sessions will be in relation to the above mentioned planned visits at the hospital. The first session will be delivered approximately 2 weeks before the operation and the last one 3 months after the operation. Each session will be approximately 45 min in length. The patient education will be delivered by one of three physiotherapists with several years of experience in treating patients with TKA and a special interest in the CBT area. The three physiotherapists have participated in a 3-day training program delivered by two psychologists specialized in cognitive behavioral therapy and pain management. The patient education is developed together with the two psychologists and the three physiotherapists. The intervention is pilot tested on 3 patients with high pain catastrophizing score before we started including patients.

The same physiotherapist will follow the patient through all the 7 sessions. To make sure that the physiotherapists will all deliver the intervention in the same way they will be observed by each other on a regular basis.

### Content

The three physiotherapists will follow a pre-specified manual containing the content of each of the seven sessions. Though the manual will leave some flexibility to discuss the patient’s individual needs and problems in each of the sessions. The content of the manual is inspired by Rolving et al. [30]. In the first session, the patient will be handed out a patient hand-book containing all the key points from the sessions and material for the homework. Further, they will receive an mp3 player with different relaxation and mindfulness exercises and a pain diary. The content of each of the seven sessions is described in Table 1.

**Table 1 Tab1:** An overview of the content of each of the seven sessions in the cognitive-behavioral intervention

Session/time	Focus and skills
1. session	Introduction to the patient education.
2 weeks preoperative	Causes and consequences of pain. Different types of pain.
	Introduction to the cognitive triangle – The link between thoughts, feelings, bodily reactions and behavior.
	*Homework*: Identify and write down thoughts in relation to painful or stressful situations.
2. session	Active and passive coping strategies.
1 week preoperative - relatives are invited to participate	How to cope with pain and distress in relation to family, relatives and work.
	The consequences of fear avoidance and the link between activity and pain.
	Relaxation and mindfulness exercise.
	*Homework*: Identify and write down your own coping strategies when in pain or distress. Relaxation and mindfulness exercise.
3. session	Appropriate activity management – activity pacing.
3–5 days preoperative	Pleasant activity scheduling.
	Goal setting.
	Introduction to pain diary.
	*Homework*: Identify five activities you used to enjoy and would like to do again.
4. session	Summary of learned skills from previous sessions.
During hospitalization	Goal setting for the next 14 days.
1–2 days postoperative	Appropriate rest and activity.
	*Homework*: Use the pain diary the next 14. days.
5. session	The cognitive triangle – The link between thoughts, feelings, bodily reactions and behavior.
14 days postoperative	Learning how to change negative automatic thoughts and catastrophic pain-related thoughts into more realistic thoughts by using cognitive restructuring techniques
	Pleasant activity scheduling and activity pacing.
	*Homework*: Use pacing techniques and pleasant activity scheduling to restart daily activities and hobbies. Write down how it affects your mood and pain level.
	Identify and write down troubled thoughts and how they affect your feelings, bodily reactions and behavior. Consider alternative realistic thoughts.
6. session	Restructuring of inappropriate thoughts.
4 weeks postoperative	Working with the patient’s individual problems.
	Goal setting for the next 2 months.
	*Homework*: Identify catastrophic and negative thoughts and try to change them to alternative more realistic thoughts.
7. session	Brush up from the 6 previous sessions and a reflection of which coping techniques and cognitive techniques the patient can and will use in the future
3 months postoperative	How to manage and control flare-ups
	Plan for the future

All sessions begins with questions and a talk about the homework from the previous session

The patient education involves three main components: a) education about pain and the role pain coping skills can play in pain management, b) systematic training in a variety of cognitive and behavioral pain coping skills, c) training in how to apply learned coping skills to real life situations that are particularly challenging to the patient.

The goal of the patient education is to teach the patients about pain in order to gain a better understanding of how cognitions and behavior affect the pain experience. We want them to understand the link between thoughts, feelings, bodily reactions and behavior and to realize their own role in controlling their pain experience. The patients shall learn to use appropriate coping strategies such as activity pacing and pleasant activity scheduling to increase their activity level and observe the resultant impact on their pain related cognitions. Additionally, the patients will be trained in cognitive restructuring. Using techniques drawn from cognitive therapy the patients will be taught how to identify irrational, maladaptive and catastrophic related thoughts that contribute to pain and how to replace them with alternative rational and more positive thoughts. Each patient will learn about their own early warning signs of setbacks and potential high risk situations and how to use the coping skills learned in the seven sessions to deal with future challenges.

